# School-based prevention of teacher and parental violence against children: Study protocol of a cluster-randomized controlled trial in Tanzania

**DOI:** 10.1186/s12889-024-19888-7

**Published:** 2024-08-31

**Keywords:** School violence, Teacher violence, Parental violence, Family violence, Children, Public schools, Primary schools, Cluster-randomized controlled trial

## Abstract

**Background:**

Violence against children at home and at school is particularly prevalent in Africa and is associated with adverse and persistent health effects on children. The violence prevention intervention *Interaction Competencies with Children* -* for Teachers* (ICC-T) is an effective tool to reduce violence against children by fostering teachers’ non-violent communication and interaction skills. To enhance these effects, in the present study, ICC-T will be extended to parents (ICC-P) aiming to increase children’s experience of consistent behavior and application of non-violent discipline strategies between teachers and parents.

**Methods:**

To investigate the effectiveness of the school-based combined implementation of ICC-T and ICC-P, a cluster-randomized controlled trial with 16 primary schools in the urban district of Morogoro in Eastern Tanzania will be conducted. Both quantitative (structured interviews) and qualitative (focus group discussions, in-depth interviews, evaluation forms) methods will be used to investigate the effects on teachers’ and parents’ violence against children in home and school settings. The intervention implementation will be accompanied by a comprehensive process evaluation to assess the implementation quality of and participants’ engagement with ICC-T and ICC-P. Potential downstream effects of violence reduction will be investigated by assessing the children’s mental health and well-being.

**Discussion:**

The present study aims to provide evidence for the feasibility, acceptability, and effectiveness of the school-based combined implementation of ICC-T and ICC-P to reduce teacher and parental violence against children and contribute to children’s well-being in home and school settings.

**Trail registration:**

The clinical trial was registered at ClinicalTrials.gov (ClinicalTrials.gov, 2024) under the identifier NCT06369025 ([name], Preventing Physical and Emotional Violence by Parents and Teachers in Public Schools in Tanzania (ICC-T/ICC-P_Tanz) (PreVio), 2024) on April 17, 2024.

## Background

By ratifying the United Nations (UN) Conventions on the Rights of the Child [1], violence against children has been outlawed worldwide. Nevertheless, more than 1.7 billion children – 75% of all children worldwide – experience violence in their upbringing [2]. In school and at home, teachers and parents appear to use violence against children in order to regulate or correct misbehavior [3, 4]. These violent disciplinary measures may be physical acts of violence and include beatings with the use of hands or objects, shaking, pinching or kicking children as well as emotional acts of violence including harsh verbal reprimands as well as public humiliation [5, 6]. Several studies suggest that violence against children is associated with lower quality in the child–adult relationship, negative mental health outcomes, and behavioral and emotional problems that begin in childhood and may persist through adolescence and adulthood [7–11].

### Many children are still regularly subjected to violent discipline both at home and school

Prevalence rates of violence at home and in school are higher in poorer countries [12], with particularly high rates in Africa [4, 13, 14]. With violence prevalence rates of more than 89% at home and in school in East and North African countries [2, 6], prevalence rates in Tanzania [3, 14] are representative for these countries. Specifically, about 75% of children in Tanzania report having been slapped, kicked, beaten up, pushed or threatened with a weapon by relatives, parents, or guardians during their childhood [4, 15, 16]. This high rate of violence against children by parents or guardians in Tanzania reflects the current legal situation in this country, with laws permitting the use of corporal punishment in all setting as justifiable means of correcting children’s behavior [8, 17].

In school settings, violence is still legally accepted in 64 countries worldwide, mostly comprising Asian and African countries with middle to low income [18]. Systematic reviews indicate that in low- and middle-income countries, 70% to 100% of children experience physical violence by teachers, particularly in Africa [6, 19]. These reviews also reveal that physical violence in schools even remains high in countries where corporal punishment has been banned by law. Similar to the reported rates for physical violence, the prevalence rates for emotional violence perpetrated by teachers against children are reported to be high in countries across the world [20–22]. In Tanzania, 99% of teachers of secondary schools reported that they have used emotional violence against a student at least once in the past year [16] and more than 95% of primary school teachers had used at least one or more forms of emotional violence in the past one month [23].

### Teachers and parents justify physical and emotional violent discipline to maintain children’s discipline

Parents’ or teachers’ use of violence against children is influenced by various interacting factors including structural, institutional, community, interpersonal, and individual factors [24]. Community social norms and culture appear to promote parents’ and teachers’ use of physical and emotional violence to correct or shape children’s behaviors [13]. Specifically, both parents and teachers reportedly share the belief that the use of physical and emotional violence is a way to demonstrate dominance over children and thus gain their respect for educational intentions [4, 23]. Moreover, the use of violence by parents and teachers has been associated with a lack of knowledge of non-violent alternatives to dealing with children’s misbehavior or good parenting skills [4, 25], personal experiences with violence in their upbringing [23], and high-stress working conditions and economic strain [26, 27].

### Effects of violence on child development

Evidence from clinical and developmental psychology shows that violence experienced in childhood is associated with toxic stress [28]. It is well established that stress during childhood affects the developing brain and establishes permanent alterations in psychosocial and physical health. These alterations can undermine learning and affect children’s behavioral, social, and emotional functioning. Several studies suggest that violence against children is associated with lower quality in child–adult relationships, negative mental health outcomes, and behavioral and emotional problems that begin in childhood and may persist into adolescence and adulthood [7–11]. Violence against children has also been associated with impaired cognitive functioning [8, 29, 30]. Studies on children’s and adolescents’ victimization focusing on family settings and studies focusing on school settings find comparable negative effects of physical violence including physical injury and even death, poor academic outcomes, mental health, and behavioral problems [6, 19, 31–34]. Thus, violent discipline as an educational measure is counterproductive to the children’s upbringing parents’ and teachers’ beliefs about positively shaping children’s behavior. In fact, it physically, emotionally and socially harms children.

### Violence reducing interventions targeting parents and teachers

The strikingly high prevalence of violence against children calls for concentrated efforts to reduce and stop violence at different levels including: individual, family, institutional, and societal levels at large. Researchers suggest legislative reforms to prohibit and sanction the use of violent discipline in the family and at school [35]. In line with this, the UN Sustainable Development Goals 2030 initiatives including goal 16:2 [36] and the African Charter on the Rights and Welfare of the Child [37] are likely to have impacts on political changes and legal reforms in African countries and other parts of the world. In parallel, programs that promote awareness about the various detrimental effects of child violence, but also strengthen reporting and referral structures for victimized children, and provide positive parenting skills emphasizing non-violent discipline strategies to parents, caregivers, and educators’ practitioners are needed.

Regardless of global and continental initiatives, however, there is a pressing need for preventative interventions targeting the family and school level to eliminate violence against children, particularly in African countries where violence against children is rampant [18]. To this end, teachers and parents need to be made aware of the adverse and lasting effects of their use of violence against children, learn and use non-violent discipline strategies in their daily routines, and change their personal beliefs. Interventions addressing the perpetrators’ beliefs and behaviors are thus urgently needed to keep a child safe at home and at school.

Only two programs that equip teachers with non-violent action alternatives have been implemented and rigorously evaluated in Africa: the Interaction Competencies with Children – for Teachers (ICC-T) [3, 5, 38, 39] and the Good Schools Toolkit [40]. The latter program focuses on extensive staff training and coaching on non-violent disciplinary methods and involves classroom activities for students. In follow-up evaluations, students assigned to the intervention schools reported a significant decrease in the frequency of past-week physical violence use by teachers, compared to students in control schools [40]. The ICC-T approach is particularly feasible in low-resource contexts as the costs for the implementation are comparably low. The core component of the program is a manualized one-week training workshop focusing on the basic competencies in the work with children, including non-violent action alternatives. ICC-T is very flexible and participatory as it engages the participants in tailoring the program according to their knowledge and needs. This makes ICC-T successful with people from various countries and cultural or educational backgrounds. The ICC-T program is designed in such a way that local professionals with a background in social work, psychology or the like are also able to implement the program with teachers [41]. In cluster-randomized control trails (CRCTs) in Tanzania and Uganda, it was shown that teachers who participated in ICC-T applied significantly less violence against children compared to teachers in the control group. This was not only reported by the teachers themselves, but also by the students who were blinded with regards to the treatment allocation of their school [3, 42].

However, children do not only experience violence at school but also in their home. In order to effectively protect children from violence in their upbringing, preventive work with those who most frequently and intensively use violence against children, i.e. parents and teachers, is of central importance. A number of previous studies have evaluated the benefits of parenting programs that emphasize the use of non-violent discipline techniques [43, 44]. One example is the Parenting for Lifelong Health (PLH) [45] program which was developed, delivered, and tested mainly in South Africa [46], but with adapted versions also in other African countries including Tanzania [47] and Kenya [48]. The program focuses on preventing child maltreatment and involvement in other forms of violence at the family level. The experimental evaluation of the program pointed to improvements in the parent–child relationships, child attachment, and of the cognitive and socio-emotional development of children as well as to reductions in the family mental health distress [46]. The Irie Homes Toolbox is another parenting program for families in low- and middle-income countries [49], with studies documenting increases in parents’ friendly interaction with their children and decreases in the use of harsh punishment among parents who have received the intervention [50, 51]. These interventions focus on parenting skills. Yet, interventions focusing on stopping or reducing violent discipline at home and school by equipping parents and teachers with non-violent discipline strategies and addressing changes in personal beliefs and questioning social norms are also highly needed to keep a child safe at home and school.

### Aims and Objectives—children experience consistency in the behavior and application of non-violent discipline strategies between teachers and parents

Following the socio-legal research’s approach to begin at school-level to reduce violence against children [35], a school-based approach including both teachers and parents has three key advantages: a) Children experience consistency in the behavior and application of non-violent discipline strategies between teachers and parents, b) parents of different social, economic, and educational backgrounds can be motivated to participate in the intervention, and c) using the existing infrastructure of schools reduces costs and improves the reach and scalability of the program. In line with this, researchers also argue that parents and teachers learn from one other [3].

This research project follows up on extensive evidence on the feasibility and effectiveness of ICC-T [52] and on evidence from one study of ICC-P which was conducted in an uncontrolled design with parents [53]. By combining ICC-T and ICC-P in a school-based intervention, the present study uses a unique and novel intervention approach as it will focus on reducing violence at family and school level at the same time. The intervention approach will enhance teachers’ and parents’ interaction competencies with children. This study is expected to improve the holistic environment for children at school and at home. We hypothesize that the school-based preventive intervention will significantly reduce the use of parents’ and teachers’ physical and emotional violence against children and will have a positive impact on children’s well-being and mental health.

## Methods

### Design

We will use a two-armed school-based CRCT including 16 primary schools in the region of Morogoro, Tanzania. Eight of 16 selected schools will be randomly allocated to the intervention group, which will receive the school-based training (ICC-T for teachers, ICC-P for parents), and the other eight schools will be allocated to the control group without any intervention. The study will include two data collection phases, one baseline assessment before the intervention allocation and one follow-up assessment approximately three months after the allocation and delivery of the intervention (c.f., study flow chart in Fig. 1 & time-line in Table 1).

**Fig. 1 Fig1:**
[figure not shown]
Flow chart of the study design

**Table 1 Tab1:** Study time-line

	Study period		
	Baseline (t_0_)	Intervention (period: 6 weeks)	Follow-up (3 months after intervention; t_1_)
Allocation (after baseline)	x		
ICC-T & ICC-P training		x	
Primary outcome: violence by teachers & parents	x		x
Secondary outcomes (i.a.; stress)	x		x
Process evaluation		x	
Focus group discussions		x	
In-depth interviews			x

### Study setting and sampling

This intervention study will be implemented in public primary schools in Morogoro in Eastern Tanzania, particularly in the urban district of Morogoro. Based on geographical locations of districts in the Morogoro region, the Morogoro urban district council was purposely selected for the study for feasibility reasons. For randomization, we used random.org [54]. First, we created a list of all eligible schools (38) fulfilling our inclusion and exclusion criteria from all wards (smallest administrative unit) located within the urban district of Morogoro. Second, based on our a priori power analysis, we randomly selected 16 wards and one school in each ward. We selected one school from each ward to avoid cross-over effects between the study conditions due to proximity of schools. Third, pairs of schools were formed due to primarily logistical reasons: Due to the short funding period (12 months) of this research project, the intervention will be delivered school by school. Once the first pair of schools has completed the baseline assessment, the random allocation assigns one school to the intervention and the other to the control condition and the implementation of the intervention starts directly after allocation. The allocation of the schools will be performed by the research team witnessed by two teachers from each school.

#### Schools

To be eligible for inclusion in the study, the schools have to meet the following criteria: The school is a public primary day school within the Morogoro urban district and is a mixed-gender and uniform language (Swahili) school. Public primary schools are state owned school. Thus, they are guided by Tanzania education policy including free education and the guideline for violent discipline. The school has at least 45 students in the selected grade. However, if the selected school has less than 45 students in the selected grade, then it will be combined with a nearby selected public primary school which must be within 15 km (km) from the respective school with too small class size. An equal number from each school cluster will be selected to be invited to participate in the study. The school must have at least 25 but no more than 50 employed teachers. The upper limit of 50 teachers is due to difficulties to providing the intervention. In case of less than 25 teachers, the selected school will form a school cluster together with another near-by (i.e., within 15 km) public primary school, with all teachers of both schools will be included in the study.

#### Participants

In this study, students, their parents, and teachers will be assessed at baseline and follow-up stage. The research team will cooperate with the district educational office to receive the name and ward locations (administrative division of a district) of the schools. To recruit teachers, the research team will collaborate with the head of school from the selected school and invite all teachers employed at the school. In cooperation with the collaborating teacher in the selected school, the research team will select 45 students from fifth school grade to participate in the study. Parents of the selected students will also be invited to participate in the study. The research team in collaboration with the school management will prepare letters for the parents of selected students to participate in the study. The sealed letters will be given to the student to send to his or her parents. In addition, the school management will send a text message or call the parents to consider the invitation.

Inclusion criteria for students are being enrolled in fifth school grade of a public primary school within the selected schools. Further students’ inclusion criteria are being of age between 9 and 13 years and living with their caregiver or parents. Exclusion criteria for students are severe mental disabilities that make it impossible to follow the interview questions. Inclusion criteria for teachers is to be employed at an eligible school. Exclusion criteria for teachers are acute intoxication of alcohol, drugs, or any other substance which makes it impossible to follow the interview questions. Inclusion criteria for parents are that their child is participating in the study and is enrolled in a study’s eligible school. Being a parent is understood as being the social parent currently taking care of the child independent of the biological relationship to the children. Thus, a parent can be biological parents, step-parents, foster parents, relatives, etc. The parents have to live with the child and in reachable distance to the child’s school. Exclusion criteria for parents are severe mental disabilities and acute intoxication of alcohol, drugs, or any other substance that make it impossible to follow the interview questions.

*A priori* sample size and power analyses using The Shiny CRT Calculator [55] for the CRCT with pre-post assessment was conducted [56] with a critical significant level of 5%, a power of 80%, an expected moderate effect size of ƒ = 0.25, and an assumed intra-class correlation coefficient of .05. Previous ICC-T trials in Tanzanian secondary schools revealed moderate to large effects on student-reported and teacher-reported violence by teachers, respectively [3, 4, 39, 53]. Assuming no dropout at the school level and accounting for potential dropout on the participant level of 25%, and eight clusters per arm, 25 to 28 participants within a cluster would result in sufficient power. To account for parents’ response rates that are expected to be lower than 100%, parents from 45 randomly selected students will be invited to participate. Based on an expected approximated 85% response rate of invited mothers and 65% of invited fathers, 38 mothers and 29 fathers are assumed to participate in the study. In addition, 25 teacher per school will be included in the present study. This results in a sample size of 720 students, 608 mothers, 464 fathers and 400 teachers across 16 schools. Based on these assumptions, an *a priori *power of ß = .94 for students, for mothers ß = .90, for fathers ß = .82, and ß = .76 for teachers was calculated.

### Procedures

Before data collection, research assistants will be selected by the research team and trained on data collection procedures in a five-day-workshop followed by a one-day-pilot run. Research assistants will be recruited based on the following characteristics: holding at least a bachelor degree from university and being fluent in English and Swahili language. Having prior experience in research projects on social, education, and/or health related matters is an additional advantage. All research assistants will remain blind as to whether the school was assigned to the control or intervention group.

Before data collection, informed consent of participants will be collected. The research team will explain the objectives of the study to the selected students and will provide them sealed letters of invitations for both parents to come to school. Upon parents’ arrival to school, the research team will explain the objectives of the study, and provide them with the study information sheets and the informed consent forms. Parents must read the study information themselves or with help of the research team if they are not able to read and write. Parents will then sign a consent form holding information on the aims of the study, confidentiality of the data, and the rights to withdraw from the study at any point in time during the progress of the study and without any negative consequences for participation. In addition, parents will have to provide written consent to allow their children to participate in the study. With parent’s permission and prior to the interview, the research team will inform the child orally and will ask the student if he or she is willing to participate in the study. Teachers will individually be invited to a discrete and quiet place within the school premises and be given detailed written and oral information on the aims of the study, confidentiality of their data, and their rights to withdraw from the study at any point in time during the progress of the study and without any negative consequences. Teachers will sign the consent form prior to starting the interview.

For data collection, baseline and follow-up assessments will include structured interviews for students, parents, and teachers. Participants will be interviewed by trained interviewers in the local language (Swahili). In the interview, the interviewer will directly enter participants’ responses into an Android tablet using the survey tool OfflineSurveys Pro version 1.81, based on Limesurvey version 3.27.30. The interview holds standardized introductions and administration procedures to ensure high objectivity and reliability during the data assessment. To ensure participants’ full understanding, all interviews and communications will be conducted in Swahili language. Swahili versions of the instruments that have been translated by independent translators following the scientific guidelines [57] will be used. At the end of each interview parents will be compensated (five thousand Tanzanian shillings) for their transport.

The assessment procedure will be repeated in the same way approximately three months (12 weeks) after the complete delivery of the intervention. Given the nature of the interventions, all participants will be masked during baseline assessment, however, participants will be unmasked at follow-up assessments. Nevertheless, assessors will be blind throughout the study as the interventions only target parents and teachers.

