#### Intervention procedures

Trained facilitators with well-defined background in psychology and adult-teaching will implement the ICC-T and ICC-P interventions within the premises of the selected schools. Eligible research assistants will work closely with trainers throughout the intervention. Participation in ICC-T and ICC-P respectively will be free of charge for all participants. Participants will be provided with food (breakfast & lunch) and beverages during training. Information explaining in detail the training procedure and topics will be given to each participant.

The training of parents will take place over three consecutive Saturdays and one refresher day delivered after six weeks. ICC-P will be implemented for both female and male parents in groups of 20 to 25 participants. The parents will be individually invited for training and will have gender-separate workshops on the first two workshop days with the intention to maximize participation of female and male parents [62] and to encourage parents to freely express their beliefs about discipline measures used with their children. On the third and fourth day, female and male parents will participate jointly in one training group as they will be trained on alternative discipline and good parenting skills. Teachers from the selected schools will be trained in ICC-T in groups of approximately 25 participants on five consecutive days in a week during school holidays in 2024. All trainings will take place within school premises.

To monitor the fidelity, acceptability, and feasibility of the training, a process evaluation will be conducted during the training sessions of ICC-T and ICC-P. The process evaluation will utilize standardized evaluation forms completed by trained research manager observing the program sessions (rating participants’ engagement & facilitators’ performance) and standardized reflection forms completed by facilitators after each session (rating their satisfaction with the session and specific activities covered). Furthermore, for each training day, five randomly selected participants will be asked to fill out a purpose-built questionnaire on their perceived comprehension of that day’s training content and the method used by the facilitator for delivering the content during that day. At the end of the workshop, all participants will evaluate the session content, the methods used, and the performance of trainers using a standardized questionnaire.

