#### Control

There will be no training delivered to participants from control schools. Data will be assessed at baseline and follow-up with the same procedure in control and intervention schools. During the present study, the control schools will not be part of any other, similar interventions.

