#### Measures against *bias*

The risk of bias will be minimized and the validity of the findings will be increased through several methodological strategies. First, randomly sampling schools will counteract selection bias. Second, we will use previously validated and contextually appropriate instruments and thorough training of interviewers to counteract potential reporting biases and validity threats. Third, persons involved in collecting data will remain blind to the treatment conditions of the schools as the allocation to intervention and control group will be executed at the cluster level by research team members not collecting data. Fourth, carrying out analyses of data on the level of groups as randomized (intent-to-treat) will avoid incomplete accounting of participants and outcome events.

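### The blinding claimed for all research assistants is contradicted for those who support the training, and the reasons given do not support it for those who interview adults

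*Protocol article*

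**What the plan says.** The protocol article claims blinding in three places.

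- **Procedures, on research assistants.** They are recruited for data collection: "research assistants will be selected by the research team and trained on data collection procedures in a five-day-workshop". Of this pool it says: "All research assistants will remain blind as to whether the school was assigned to the control or intervention group". No exception is made.
- **Procedures, on assessors.** After noting that participants will be unmasked at follow-up, it continues: "Nevertheless, assessors will be blind throughout the study as the interventions only target parents and teachers".
- **Measures against bias.** The third of four measures is that "persons involved in collecting data will remain blind to the treatment conditions of the schools". The reason given is that allocation is carried out by team members who do not collect data.

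Other sections describe what the assistants do and where.

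- **Intervention procedures.** "Eligible research assistants will work closely with trainers throughout the intervention", and "All trainings will take place within school premises".
- **Control.** "There will be no training delivered to participants from control schools".
- **Procedures, on who is interviewed.** "baseline and follow-up assessments will include structured interviews for students, parents, and teachers".

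**The concern.** The article describes one group of research assistants, trained for data collection and all blind, and then places some research assistants beside the trainers. Both statements cannot be true of the same people. The justification for assessor blinding is also weak, because it names as the only targets of the intervention two of the three groups that the assessors interview.

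The primary outcomes are reports of violence by teachers and parents, given by children, parents and teachers in face-to-face interviews, with the interviewer entering the answers. One kind of answer is plainly the more desirable. Participants are unmasked at follow-up, so assessor blinding is the main remaining safeguard at the point of measurement. If it is reported as written, readers will credit the trial with protection against detection bias that its own procedures do not secure.

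**Working it through.** No arithmetic applies, and there is no figure in the plan to reproduce. The check sets the statements side by side.

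**Step 1. Can an assistant support the training and stay blind?**
- Training takes place at the schools (Intervention procedures).
- Control schools get no training (Control).
- Trainers at a school therefore identify it as an intervention school, and an assistant working closely with them knows the arm.
- Procedures says that all research assistants stay blind. That cannot hold for this group.

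**Step 2. How far does that knowledge reach?**
- Under Study setting and sampling, schools are paired, and after the pair's baseline one school goes to each arm.
- Knowing the arm of one school therefore gives the arm of its partner. The assistant is unblinded for the pair.
- Baseline interviews in a pair precede its allocation, so the problem lies at follow-up.

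**Step 3. Does the reason in Procedures support assessor blinding?**
- Premise: only parents and teachers receive the intervention.
- Parents and teachers are interviewed at follow-up and are by then unmasked.
- Two teachers from each school also witness the allocation (Study setting and sampling), so some interviewees know the arm directly, in control schools as well.
- The premise can support blinding of an interviewer who sees only children. It cannot support blinding of one who interviews trained adults.

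**Step 4. Does the reason in Measures against bias support it?**
- It says that those who allocate do not collect data. This settles who performs the allocation. It says nothing about what data collectors learn afterwards, from supporting the training or from interviewees.

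**Result**

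| Staff | Status of the blinding claim |
|---|---|
| Assistants who support training | Contradicted by the text |
| Interviewers of parents and teachers | Not supported by either reason given |
| Interviewers of children only | Arguable, but no section provides for such a group |

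**The case against.** The best defence rests on one word. Only *eligible* assistants work with the trainers, which allows for a subset kept away from interviewing. Elsewhere the article speaks of trained interviewers and of persons who collect data, and it never says that an assistant who helped at a training later interviews at follow-up. Some roles are separated: a research manager observes the sessions, and allocation is done by people who do not collect data. A journal article may leave the staff rota to the full protocol. The interviews are also structured, with standardized administration, fixed response options and direct tablet entry, so an interviewer has limited room to influence answers.

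Much of this stands. That the research assistants are the interviewers is an inference from their data-collection training. A reader might infer that blinding does not exist at all in this trial, but the documents do not show that: meeting unmasked adults puts blinding at risk without proving that every interviewer becomes unblinded. A reader might also infer that the arm is known before the children are interviewed. The article gives neither the order of follow-up interviews nor the assignment of interviewers to respondents, so that is not supported either.

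The defence does not remove the contradiction. *Eligible* is not defined, no section separates training support from interviewing, and even with a separate subset the statement about all research assistants would be wrong. Standardized interviews lessen the possible influence but do not make the blinding statement true.

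**Conclusion.** The concern holds in a limited form. The stated blinding is contradicted for assistants who support training, and the reasons given do not support it for those who interview parents and teachers. For child reports it remains arguable, because children are not trained, but nothing in the article protects it.

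The size of any resulting bias cannot be derived from the documents. They do not give the number of assistants, how many support training or at which schools, or who interviews whom. Any percentage of the planned effect would be invented. The outcomes exposed are the interviewer-administered follow-up reports, including the primary ones, most clearly the parents' and teachers' own.

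The conclusion rests on two readings: that research assistants conduct the interviews, and that those working with trainers do so at the schools being trained. If the full protocol separates the roles, the first contradiction becomes an error of wording. The failure of the reason given in Procedures would remain.

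**What to change.** Reconcile the statements in Procedures, Intervention procedures and Measures against bias as follows.

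1. **Separate the roles by pair.** An assistant who supported training in a school pair does no follow-up interviews at either school of that pair. Separation by school is not enough, since one school's arm reveals the other's.
2. **Protect the child reports.** Within each pair, complete all follow-up child interviews at both schools before any adult interview. Alternatively, use different existing interviewers for children and for adults.
3. **Record unblinding.** After each interview the assessor notes whether and when the allocation became known. Report this by arm, descriptively. Do not make the exclusion of unblinded interviews an effect analysis: unblinding happens after randomization and is likelier in the intervention arm, where participants have training to mention, so exclusion could itself introduce selection.
4. **Limit the claim.** Replace the statement that assessors are blind throughout the study with one naming the staff and outcomes for which blinding is actually protected, and remove the two reasons that do not support it.

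The cost is a scheduling constraint on the interviewer rota and one extra item per interview. The number of assistants is not given, so the sponsor should check that the rota can carry steps 1 and 2, given the 12-month funding period and school-by-school delivery. If it cannot, step 4 still applies, with a correspondingly narrower claim.
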